#### Systemic Vascular Resistance and Vascular Function

Vascular dysfunction (increased arterial stiffness and endothelial dysfunction) is associated with worse aerobic exercise capacity (76–78). This is likely related to impaired skeletal oxygenation and muscle blood flow rather than the contribution of endothelial dysfunction to increased systemic vascular resistance (elevated afterload) in the setting of limited preload reserve (41, 79). Elevated systemic vascular resistance is likely a secondary phenomenon required to maintain adequate blood pressure in the Fontan circulation at rest and during exercise (80).

#### Sex

Data from the Australian and New Zealand Fontan Registry has shown that the male sex is associated with an increased risk of premature death or transplantation (1, 81). Consistent with this observation in people with a Fontan circulation, male sex is a factor associated with lower aerobic exercise capacity (relative to age and sex) and progressive exercise intolerance (26, 49). The sex differences in aerobic exercise capacity may be related to reduced muscle mass compared to healthy controls, which is likely more pronounced in males (especially during puberty), and the inability of the single ventricle to support the increased metabolic demands of the greater absolute skeletal muscle mass in males.

#### Hypoxemia and Cyanosis

Cyanosis or hypoxemia is common in people with a Fontan circulation. It is unclear whether a patent fenestration is associated with improved aerobic exercise capacity as a result of increased ventricular filling or if the establishment of a right-to-left shunt and subsequent hypoxemia will impair it; data on the effects of fenestration closure are inconsistent (82–84). However, fenestration closure has been shown to improve ventilatory efficiency (83), which may decrease dyspnea perception during submaximal exercise.

Paradoxically, lower hemoglobin is associated with better aerobic exercise capacity (14). A similar relationship was reported with lean mass, which is inversely correlated with hemoglobin (85). This is probably because elevated hemoglobin reflects a compensatory erythrocytosis in the setting of low oxygen saturation. This contrasts with the findings of Kodama et al., who reported a positive correlation between peak VO_2_ and hemoglobin (86). Regardless of the reported conflicting associations, the contribution of arterial desaturation to reduced aerobic exercise capacity is minimal, explaining <5% of the variance in peak VO_2_ (40).

#### Skeletal Muscle Function

Handgrip strength, dynamic muscular strength, and muscular endurance have all been reported to be lower in people with a Fontan circulation than in healthy, age-matched controls and are associated with reduced skeletal muscle mass (85, 87–89). In a series with a heterogenous sample of CHD lesions (30% Fontan), when strength was indexed to lean mass, there was no difference in isometric strength compared with healthy controls (90). This may suggest that the reductions in muscle strength reported can largely be attributed to the reduction in lean mass that we and others have demonstrated (85, 89, 91). Beyond generalized muscle weakness (92), peripheral skeletal muscle blood flow and ergoreceptor function appear to be abnormal (89, 93), and this is likely accompanied by a shift in muscle fiber type (to type IIb), similar to the findings in acquired heart failure. Furthermore, impaired skeletal muscle oxidative capacity has been shown using MRS P^31^ spectroscopy, and delayed muscle oxygen uptake kinetics denote potential muscle metabolic abnormalities (21, 94). The combination of these skeletal muscle abnormalities likely result in the early onset of metabolic acidosis, premature fatigue during exercise, and consequently impaired aerobic exercise capacity.

#### Body Composition

##### Skeletal Muscle Mass

Even in relatively young people with a Fontan circulation, there is a high prevalence of skeletal muscle deficit compared to age-sex matched controls (21, 91). Although myopenia (low muscle mass) is prevalent across many CHD lesions, it is likely those with a Fontan circulation experience a greater degree of lean mass deficits. The causes of lean muscle deficits are poorly defined, but in the Fontan circulation, relative deconditioning, chronically elevated central venous pressure, physical inactivity, neurohormonal activation, and altered blood flow are likely contributing factors. To highlight this pathophysiological difference to sarcopenia (age-related muscle deficits) and low lean mass in other CHD lesions, Tran et al. described the term Fontan-associated myopenia (appendicular lean mass index Z-score < −2) (85). Low lean mass in the setting of Fontan physiology is particularly concerning, given the strong correlation between skeletal muscle mass and exercise stroke volume and/or aerobic exercise capacity (21, 89, 95, 96). This can be attributed, inter alia, to improved cardiac preload—greater skeletal muscle mass decreases venous compliance and squeezes a greater volume of blood back toward the pulmonary vasculature and heart (97). Leg muscle contractions may also generate a pulsatile flow profile in the pulmonary vascular bed (98).

##### Obesity and Adiposity

A higher BMI is associated with lower aerobic exercise capacity in people with a Fontan circulation. High levels of adiposity—particularly in the thoracic region—may impair the function of the respiratory bellows. The Pediatric Heart Network Fontan III study showed that patients in the lowest tertile, based on percent predicted peak VO_2_, were more likely to be overweight or obese (26). However, defining “healthy” weight status using BMI in this cohort is problematic because the high prevalence of lean mass deficiency conceals the presence of increased fat mass when BMI is used as a surrogate of adiposity (85). Although the adverse effects of obesity will likely impair aerobic exercise capacity (14), further research using reference measures of lean and fat mass should be conducted to better characterize the implications of obesity on Fontan physiology.

#### Respiratory Muscle Dysfunction

Extending beyond the effects that respiratory muscle weakness may have on dynamic lung function, it also contributes to an increase in motor command output, resulting in a greater sensation of breathlessness during exercise (99). Furthermore, in the setting of limited cardiac reserve, the redirection of blood flow from the exercising skeletal muscles to the respiratory muscles (“metaboreflex”) promotes premature fatigue and profound impairment in aerobic exercise capacity. These mechanisms may, in part, explain the association between respiratory muscle function and aerobic exercise capacity in Fontan patients (92).

At rest, Fontan physiology is heavily dependent on respiration to promote ventricular filling. Theoretically, it would be expected that improving inspiratory muscle strength would augment the respiratory muscle pump and ventricular filling. While inspiratory muscle training has been shown to improve ventilatory efficiency and resting cardiac output, most studies have not resulted in statistically significant increases in peak VO_2_ (100–102). This may be because the skeletal muscle pump accounts for the majority of the increase in cardiac output, with only minor contributions attributed to the respiratory pump during exercise (103). Respiratory muscle training may be beneficial in patients who specifically have clinical respiratory muscle weakness. This notion was supported by a recent randomized controlled trial, where baseline measures of maximal inspiratory pressure indicated inspiratory muscle weakness in the cohort; peak VO_2_ increased after 4 months of inspiratory muscle training (104).

#### Benefits of Exercise Training and Safety

Paradoxically, the most effective non-invasive therapy to manage exercise intolerance is exercise training (97, 105, 106). A recent review of respiratory muscle and exercise training studies in over 200 people with a Fontan circulation showed that the majority of studies resulted in improvements in peak VO_2_ (107), and increases of up to 23% (treatment effect 30%) have been shown with combined aerobic exercise and light resistance training (104). Other benefits included improvements in skeletal muscle mass, cardiac output, peripheral muscle oxygenation, and ergoreceptor function (97, 105, 106, 108–110). Importantly, some studies also show improvements in health-related quality of life (111–115).

Furthermore, long-term participation in sports, physical activity, or exercise may have direct benefits on Fontan physiology. Increasing skeletal muscle mass through resistance exercise training can enhance the function of the peripheral muscle pump and augment venous return (108). The periodic increase in volume load during exercise “stretches” the preload deprived ventricle and may attenuate the phenomenon of progressive “disuse hypofunction” (58, 116). Regular physical activity like exercise training transiently but repetitively increases pulsatile flow and recruit pulmonary vessels, which may have important implications for pulmonary vascular growth and function (97, 116). Indeed, those who participate in regular physical activity (particularly during childhood) appear to have better Fontan physiology and are more likely to exhibit a high physical performance (“Super-Fontan”) phenotype (54, 117, 118). Collectively, these mechanisms may explain the association between higher peak VO_2_ and better end-organ function, clinical outcomes, and prognosis (10, 13, 14). However, further research is required to confirm this hypothesis.

##### Safety of Physical Activity and Exercise Training

Reviews of exercise training studies in people with a Fontan circulation have not reported any serious adverse events associated with exercise training (107, 110). Undeniably, during exercise, systemic venous pressure can increase dramatically in the Fontan circulation (119). While there are some concerns related to the deleterious effects of the transient elevation of central venous pressure during exercise on end-organ function, the current evidence suggests these are unwarranted. Higher aerobic exercise capacity is associated with healthier end-organ function biomarkers, potentially reflecting decreased venous pressure, better hemodynamics, and reduced hepatic congestion (14, 54). This is further supported by a series that showed lower venous pressure and better markers of end-organ function in adult patients who increased their aerobic exercise capacity during childhood (reflecting increased physical activity levels or exercise training) (118). Together, these data should alleviate the concerns regarding safety and end-organ damage associated with chronic moderate-to-vigorous intensity exercise training, but more prospective data are needed.

## Addressing the Unanswered Questions: Rationale for the Fontan Fitness Intervention Trial—Therapies and Future Direction

The mechanisms underlying impaired aerobic exercise capacity in the setting of Fontan physiology differ significantly from other chronic cardiac conditions. Traditional pharmacotherapies used to manage exercise intolerance in the biventricular circulation are of limited utility in the Fontan circulation. Currently, exercise training has been shown to be the most effective, non-invasive therapy for improving aerobic exercise capacity in people who have a Fontan circulation (Figure 5) (105, 106, 109).

**Figure 5 F5:**
[figure not shown]
Controlled trials of non-invasive therapy to improve aerobic exercise capacity in the Fontan circulation. The percentage change in peak oxygen uptake following non-invasive therapies or placebo in Fontan cohorts are shown. The most effective non-invasive therapy is exercise training. n, non-significant; *, statistically significant; ^†^, percentage difference between groups. Kouatli et al. (120); Goldberg et al. (63); Goldberg et al. (62); Hebert et al. (64); Cordina et al. [high intensity resistance training] (108); Turquetto et al. [combined aerobic exercise and light resistance training] (104).

While this review identifies common factors that contribute to exercise intolerance (Figure 6), understanding factors associated with superior aerobic exercise capacity is also important to more deeply characterize the pathophysiology. Recent series have studied cohorts of people with Fontan physiology with normal or superior aerobic exercise capacity (14, 54, 121). We previously described a subset of young people who can achieve normal or even supranormal exercise performance (“Super-Fontan”) (121). Importantly, in this series, a proportion had unfavorable Fontan features (e.g., dominant right ventricle, pacemakers, and atriopulmonary connections), suggesting extracardiac factors play a significant role in aerobic exercise capacity.

**Figure 6 F6:**
[figure not shown]
Factors contributing to exercise intolerance in the Fontan circulation. Factors in red may be improved with exercise training.

A common characteristic of a person with a Fontan circulation who has “normal” aerobic exercise capacity is regular participation in moderate-to-vigorous intensity physical activity from a young age (54, 121, 122). Some possible mechanisms for this observation may include superior development of the pulmonary vasculature (e.g., increased pulmonary artery size), increased lower limb lean mass, higher lung volumes due to stronger respiratory muscles, and adaptive remodeling of the single ventricle due to better preload (97, 98, 106). Exercise training can systemically target components that are both distal (downstream) and proximal (upstream) to the critical “bottleneck” as well as the pulmonary vasculature itself. This makes exercise training an attractive therapy and may explain the efficacy observed compared to drug therapies that may only target a single component of Fontan physiology.

However, despite the aforementioned benefits associated with exercise training and physical activity, traditionally, most people with CHD have not received formal advice (beyond restrictions) on physical activity, sports, and exercise training during their clinical consultations (123). This may be related to the paucity of quality evidence available on safety and efficacy; most studies are based on small heterogenous samples and were without a control group. While current exercise training recommendations are available to guide clinical practice (106, 109, 124, 125), these are predominantly based on clinical experience and expert opinion. Indeed, the most recent 2018 AHA/ACC and 2020 ESC guidelines suggest that there is only moderate (level B) evidence to support recommending cardiac rehabilitation or exercise training in people with CHD (4, 126). Therefore, adequately powered, multi-center, randomized, controlled trials such as the F-FIT are required to provide high-quality (level A) evidence to conclusively support recommending exercise training in clinical practice.

Furthermore, the “traditional” model of exercise training for people living with chronic diseases requires face-to-face supervision by exercise professionals (at least initially) that are often only available at expert centers. Whilst it is likely that performing exercise training in a supervised fitness facility setting is “optimal”, this method of exercise training delivery requires high resource utilization and may not be economically feasible or practical for many people living with a Fontan circulation. In addition, traditional exercise training programs offered to people with CHD are usually designed for older adults with chronic conditions (e.g., cardiac rehabilitation), which may not be suitable for the relatively young adult CHD population. Indeed, previous studies have identified this as a potential barrier to participation (127, 128), and over half of those surveyed with CHD expressed interest in a technology-directed, home-based, exercise program (129).

The F-FIT will be one of the first phase III multi-center, randomized, controlled trials to provide high-quality evidence to “optimize” exercise training in people living with a Fontan circulation. The F-FIT will also investigate if a telehealth exercise training model (that requires less resources) can produce equivalent (non-inferior) results to a traditional supervised gym-facility-based approach.

The primary objectives of the F-FIT are to:

a) Establish the efficacy of a 4-month traditional supervised gym-based aerobic and resistance exercise training program of moderate-to-vigorous intensity on peak VO_2_ compared to usual care in adolescents and adults.b) Establish the efficacy of a 4-month physical activity program of moderate-to-vigorous intensity on peak VO_2_ compared to usual care in children.c) Evaluate if a 4-month telehealth exercise training program of moderate-to-vigorous intensity can produce comparable (non-inferior) improvements in peak VO_2_ compared to the traditional exercise training group in adolescents and adults.

Secondary objectives include:

a) Determining if participants in the exercise intervention groups can maintain changes in peak VO_2_ with remote support over an 8-month period.b) To evaluate the health economics (cost-effectiveness) of exercise training interventions based on health-related quality of life, health care utilization, and patient costs.c) To characterize the mechanisms that underlie changes in peak VO_2_.d) To characterize the physiological and neurocognitive changes associated with exercise training, including changes in cardiopulmonary testing measures, peripheral venous pressure, body composition (skeletal muscle mass, fat mass, and bone mineral density), endothelial function, neurohormonal activation, skeletal muscle oxygenation, respiratory muscle and lung function, neurocognitive and neuropsychological function, metabolites, nutritional and dietary status, liver stiffness, and cardiac function.

## Study Design and Methods

### Study Population

Participants will be recruited from the Australian and New Zealand Fontan Registry (130), National CHD Database, and eight quaternary CHD centers, including Royal Prince Alfred Hospital, Sydney, Australia; The Children's Hospital at Westmead, Sydney, Australia; Royal Melbourne Hospital, Melbourne Australia; Royal Children's Hospital, Melbourne Australia; Perth Children's Hospital, Perth, Australia; Fiona Stanley Hospital, Perth, Australia; The Prince Charles Hospital, Brisbane, Australia; and Queensland Children's Hospital, Brisbane, Australia. Advertisements will also be disseminated *via* social media, websites, and flyers to facilitate recruitment.

The F-FIT will include people with a Fontan circulation aged 10-55 years. Participants will also need to be ≥6 months post-Fontan completion, clinically stable, and on stable medical therapy for ≥3 months to be eligible. The inclusion and exclusion criteria are provided in Table 1. A two-step exclusion process will take place:

1) Based on the patient's most recent medical records, phone screening, and approval from their treating cardiologist.2) Following baseline testing.

**Table 1 T1:** Study inclusion and exclusion criteria.

**Inclusion criteria**
•People with a Fontan circulation aged 10-55 years •Medically stable and on stable medical therapy for ≥3 months •≥6 months post-Fontan completion
**Exclusion criteria**
•Planned intervention within 2 years •Mental or physical disability that prevents participation in exercise training •Current or actively planned pregnancy •Uncontrolled systemic hypertension at rest or during exercise •Clinically unstable or recent significant change in therapy (within 3 months) •Physiological stage D in accordance with ACC/AHA guidelines •COVID-19 unvaccinated individuals despite being eligible according to ATAGI recommendations •Unreliable internet connection •Current participation in structured sports or exercise training for more than 30 min, three times a week

Participants will be excluded prior to randomization during the two-step eligibility evaluation if any of the following are identified: categorized as physiological stage D, have a planned surgical intervention within 2 years, current pregnancy or actively planned pregnancy (within 1 year), mental or physical disability that restricts participation in exercise training, uncontrolled arrhythmias or (systemic) hypertension at rest or during exercise, a recent significant change in medical therapy (<3 months), and people who currently participate in structured sports or exercise training for more than 30 min, three times per week. People who are COVID-19 unvaccinated and are eligible for vaccination according to the Australian Technical Advisory Group on Immunization (ATAGI) recommendations will also be excluded.

### Randomization and Stratification

The F-FIT will involve three arms in adolescents and adults (≥16 years), and two arms in children (<16 years). Adolescents and adults will be randomized in an allocation of 2:2:1 to either a traditional gym-based exercise program (traditional group), a telehealth exercise training program (telehealth group), or usual care (control group), respectively. Children will be randomized to either an exercise training program or usual care (control group) based on a 1:1 allocation. Randomization will be stratified by: baseline aerobic exercise capacity (<65% or ≥65% predicted peak VO_2_); sex (male or female); and age (16-34 years or 35-55 years for adolescents and adults; 10-12 years or 13-15 years for children). Computer-generated, random permuted blocks will be prepared by an independent statistician in the Clinical Epidemiology and Biostatistics Unit (CEBU) at Murdoch Children's Research Institute (MCRI) and incorporated into the REDCap randomization tool (hosted by MCRI) that will be embedded in the REDCap database created for this trial. The randomization schedules will be prepared for each recruitment site.

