#### Statistical Analysis

The primary analysis will be based on intention-to-treat (ITT), including all randomized participants regardless of exposure to the allocated treatment or adherence to the trial protocol. Comparison of the primary outcome measure (change in peak VO_2_ at 4-months) between the groups will be estimated using linear regression adjusted for the stratification factors used during randomization. Results will be presented as the difference of means with a corresponding 95% confidence interval (CI) and *p*-value. Secondary outcomes at 4-months and 12-months will be compared between the groups using linear regression with adjustment for the stratification factors for continuous outcomes and binary regression adjusted for the stratification factors used during randomization for binary outcomes where results will be presented as a risk difference and corresponding 95% CI.

For each participant cohort, if the proportion of missing data for the primary outcome is more than 5%, analysis based on multiple imputation may be performed. A sensitivity analysis to compare the results of analyses restricted to participants with complete data and analyses where those with missing data are included using multiple imputation will be performed. If used, multiple imputation models will be conducted for the outcome variable, and 50 completed data sets will be imputed by chained equations, including all the participants initially randomized. The primary outcome, randomization strata variables and variables predictive of (i) missingness and/or (ii) the change in peak VO_2_ will be included in the imputation model.

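### Site-specific randomization schedules make site a working stratifier, but site is not among the listed factors that the primary and secondary models adjust for

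*Protocol article*

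**What the plan says.** **Randomization and Stratification** gives the factors: "Randomization will be stratified by: baseline aerobic exercise capacity (<65% or ≥65% predicted peak VO_2_); sex (male or female); and age", with age cut at "16-34 years or 35-55 years for adolescents and adults; 10-12 years or 13-15 years for children". Each factor has two levels. The same section says "Computer-generated, random permuted blocks will be prepared by an independent statistician", gives no block size, and closes with "The randomization schedules will be prepared for each recruitment site". Allocation is 2:2:1 in adolescents and adults and 1:1 in children.

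**Study Population** names "eight quaternary CHD centers" in four cities, two per city. It does not say how many of them recruit each age cohort.

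**Statistical Analysis** states that the primary comparison "between the groups will be estimated using linear regression adjusted for the stratification factors used during randomization". The secondary outcomes are adjusted for the same factors, and the imputation model, if used, includes the randomization strata variables. None of these sentences names the factors. Each relies on the list in the randomization section.

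**The concern.** A schedule held separately at each site limits how far the arms can differ in size within that site, which is what stratifying by site does. The list of factors nevertheless stops at three. The analysis section defines its covariates only by reference to that list, so two analysts could both claim to follow the plan and fit different primary models, one with site and one without.

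The choice has consequences if site is related to change in peak VO2. That is plausible here: testing is spread over several centers, and supervised training takes place in local facilities with different staff. Forcing balance on a prognostic factor removes its contribution from the real sampling error of the treatment difference. A model without that factor leaves its variance in the residual and reports a standard error larger than the design warrants. Intervals are then too wide and tests too cautious. The cost would fall mainly on the non-inferiority comparison of telehealth with traditional training, because superiority has power to spare on the stated inputs.

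**Working it through.** **1. The plan's own power figures** (Power Analysis: difference 10%, SD 5%, 44/44/22, 10% dropout, 85% retention)

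- Superiority, evaluable 39.6 v 19.8: SE = 5 × √(1/39.6 + 1/19.8) = 1.376. Power = Φ(10/1.376 − 1.96) = Φ(5.31), above 99.9%. This agrees with the stated minimum of 80%.
- Retention test, N = 110: SE = 5 × √[(1 + 0.85²)/44 + 0.15²/22] = 5 × √0.0402 = 1.002. Power = Φ(1.5/1.002 − 1.96), about 32%, against the stated 80%. That mismatch is a separate matter. It is relevant here only because this test has no slack to absorb standard errors that are too wide.

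**2. Which factors does the model contain?**

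| Source | Factors |
|---|---|
| Factors listed as stratifying | capacity, sex, age |
| Factors that restrict the allocation | capacity, sex, age, site |
| Factors in the model | those used in randomization, not named |

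The third row can be read as either of the first two. The first row is the natural reading, because it is the only list the article gives.

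**3. Size of the effect on the standard error**

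Let ρ be the share of outcome variance, after the three factors, that lies between sites. With allocation fully balanced within site, a model without site overstates the standard error by a factor of 1/√(1 − ρ). The article does not give ρ. For assumed values of 5%, 10% and 20%, the factor is 1/√0.95 = 1.03, 1/√0.90 = 1.05 and 1/√0.80 = 1.12. These are upper limits, because part-filled blocks balance the arms within site only approximately. At ρ = 0 there is no effect.

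**4. Cost of adding site**

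- Evaluable participants: 110 × 0.9 = 99 adolescents and adults; 70 × 0.9 = 63 children.
- Four of the eight centers are children's hospitals by name. If four centers recruit each cohort (an assumption), site costs 4 − 1 = 3 df. If all eight recruit a cohort, it costs 8 − 1 = 7 df.

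**5. Secondary check: balance in the adolescent and adult cohort**

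The three binary factors give 2 × 2 × 2 = 8 strata, or 110/8 = 13.75 per stratum. With four sites there are 32 cells averaging 110/32 = 3.4. With eight sites there are 64 cells averaging 110/64 = 1.7. The smallest complete 2:2:1 block is 5. With 32 equally likely cells, the chance that a cell reaches 5 is 26% (binomial, n = 110, p = 1/32).

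Size of the usual-care arm (target 22) in 3,000 simulated trials, with equally likely cells:

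| Scheme | SD | 95% range |
|---|---|---|
| Three factors only, blocks of 5 | 1.1 | 20–24 |
| Four sites (32 cells), blocks of 5 | 2.3 | 17–26 |
| Eight sites (64 cells), blocks of 5 | 3.2 | 16–28 |
| Simple randomization | 4.2 | 14–31 |

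Unequal sites (40/30/15/15%) with 80/20, 60/40 and 50/50 splits on the three factors gave an SD of 2.2, close to the four-site row. Blocks of 10 gave 3.3 (32 cells) and 3.8 (64 cells).

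**6. Does that drift harm the adult contrasts?**

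- Superiority with 16 controls and 46 in traditional training, after 10% dropout: SE = 5 × √(1/14.4 + 1/41.4) = 1.530. Power = Φ(10/1.530 − 1.96) = Φ(4.58), still above 99.9%.
- Retention test: the control mean carries a weight of only 0.15. In units of SD², the variance is 1.7225/44 + 0.0225/22 = 0.0402 at 44/44/22 and 1.7225/47 + 0.0225/16 = 0.0381 at 47/47/16. A smaller control arm does not hurt this test.

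**The case against.** **The wording may already cover site.** The analysis section names no factors, and if site schedules make site a stratifier, then site is among the factors used during randomization. A condensed article may also leave the covariate list to the full protocol or SAP. This part stands to a degree: site is not expressly excluded, and a document not shown may settle the matter. But the article does list what randomization is stratified by, and that list does not match the allocation it describes. The inconsistency is in the text itself.

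**The harm is conservative.** This stands. Standard errors that are too wide do not create false positives or bias the estimate.

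**A reader might infer that the cells are too small for blocking to balance anything.** The article does not support that. Part-filled blocks still limit imbalance: with blocks of 5 the SD of the control-arm size falls from 4.2 to 2.3 (about 45%) with 32 cells, and to 3.2 (about 25%) with 64. Only large blocks combined with 64 cells come near the claim (3.8 with blocks of 10, a gain of about 10%), and neither the block size nor the number of sites per cohort is stated. Nor does the 2:2:1 block argument carry over to the children, who are allocated 1:1 and could have blocks as small as 2.

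**A reader might also infer that the site lists should be replaced** by a central list or by minimization. Those are accepted alternatives, but so are site-specific lists, which protect against imbalance between sites. A central list without site would give up that protection. This is a matter of design preference.

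**Conclusion.** The point holds as a mismatch between how participants are allocated and which factors the models are said to adjust for. Site restricts the allocation, is missing from the listed factors, and on the natural reading is missing from the primary and secondary models. What follows is a primary model that is not fully settled and, if site matters, standard errors that are somewhat too wide. Validity is not threatened.

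The size of the excess depends on a between-site variance that the article does not give. The 3 df cost and the 32-cell figure assume four recruiting centers per cohort. The balance figures further assume blocks of 5. Under those assumptions, balance is weaker than with the three factors alone (SD 2.3 against 1.1) but better than simple randomization (4.2), with no material loss of power in the superiority test.

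**What to change.** 1. In Randomization and Stratification, list site as a stratification factor alongside capacity, sex and age.
2. In Statistical Analysis, name all four factors in place of the general reference. Fit site as a fixed effect in the primary and secondary models, with small sites pooled by a rule fixed before the data are seen (for example by state). Use the same list for the strata variables in the imputation model.

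The cost is a sentence in each section and about 3 df per cohort with four recruiting centers, or at most 7, against about 99 evaluable adolescents and adults and 63 children. The randomization lists need not change. If the team wants tighter balance on the three patient factors, it can reconsider the lists, but that is optional.
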